**Methods:**

In this multicenter randomized controlled trial (RCT), 120 adults with a diagnosis of AN or atypical AN (AAN) will be randomized to receive either TBT-S in addition to TAU or TAU alone. Individuals with AN/AAN and their supports will complete assessments before and after the TBT-S treatment week, and at 3- and 12-month follow-ups. The primary outcome is change in eating disorder symptomatology from baseline to the 3-month follow-up. Secondary outcomes include changes in quality of life, psychological health, body mass index (BMI), and health care utilization, as well as changes in quality of life and caregiving experience among supports.

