### Aim and objectives

The primary objective of the study is to examine the effectiveness of TBT-S when applied in conjunction with TAU. Specifically, we will measure whether TBT-S in addition to TAU will be more effective than TAU alone in reducing eating disorder psychopathology. We hypothesize that participants receiving TBT-S in addition to TAU will show significantly greater reduction in eating disorder psychopathology from TBT-S pre-assessment to 3-month follow-up, compared to controls.

Our secondary objectives will explore whether participants receiving TBT-S in addition to TAU show reduced clinical impairment, increased quality of life and lower utilization of health care services compared to participants receiving TAU only, at 3-and 12-month follow-ups. Secondary objectives also include the comparison of support experiences in terms of quality of life, psychological wellbeing, carer accommodation and expressed emotional experience of caring for a person with an ED.

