### Participants, eligibility criteria and recruitment

Adults receiving treatment for AN or atypical AN (hereafter AN/AAN as a shorthand to signify that both conditins are being discussed as a singular diagnostic entity) at a local psychiatric center and/or from other qualified treatment provider could be eligible to participate in the study. We will utilize similar recruitment procedures as employed in our TBT-S feasibility study (Stedal et al., 2023). An information pamphlet and website have been designed to facilitate recruitment, complemented by targeted advertisements on social medial platforms. Individuals express interest by sending an e-mail to the TBT-S mailbox ([contact]) hosted by Oslo University Hospital or by filling out an online form which leads to a screening call to determine eligibility.

*Inclusion criteria:* Age ≥18, body mass index (BMI) ≥ 15, currently receiving outpatient treatment for AN/AAN; self-reported medically stable (confined to physical criteria), have a minimum of one support person who can participate in the study.

*Exclusion criteria:* Intellectual developmental disorder or intellectual disability; psychotic disorder or other psychopathology that may affect or prevent participation in the study; diagnosed alcohol or other substance use disorder within 3 months prior to study initiation; ongoing inpatient treatment at the time of study enrollment (participants currently in inpatient care must be discharged and engaged in outpatient treatment before participating in the TBT-S week).

If criteria are fulfilled, informed consent from all study participants, including supports, will be obtained on an encrypted study platform (www.nettskjema.no) requiring identification and two-step authentication.

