### Interventions

#### Temperament based therapy with support (TBT-S)

Participants in the intervention arm will receive 5 days of TBT-S in addition to ongoing TAU. TBT-S is administered to three to six adults with AN/AAN together with up to four supports each. As described in the TBT-S treatment manual (Hill et al., 2022), the treatment structure consists of five consecutive days of treatment, up to seven h each day. TBT-S is delivered in a multifamily format where both individuals with AN/AAN and supports are included in all the following five treatment strategies: (1) *Neurobiological psychoeducation*. Psychoeducation helps participants recognize how AN could be understood as a biologically influenced illness, emphasizing temperament traits (e.g., anxiety, harm avoidance, altered reward processes) and mechanisms that may be involved in maintaining eating disorder symptoms; (2) *Experiential learning activities addressing eating disorder neurobiology and traits*. The experiential activities are developed to aid participants experience how traits such as cognitive inflexibility can be experienced, how to maneuver toward recovery and how supports can be of help and, importantly, they help provide insight through action rather than discussion alone; (3) *Client and support skills training*. The skills training aspect of TBT-S teaches practical, trait-aligned tools to respond more effectively to eating disorder behaviors and to ensure consistent use of skills for recovery in daily life; (4) *Meal coaching*. Participants practice skills in real time together with supports and clinicians to help tolerate distress, reduce rituals and reinforce adaptive behaviors pre, post and during meals; (5) *TBT-S behavioral agreement*. The behavioral agreement is an individually tailored written plan, developed collaboratively by the participant with AN/AAN, their supports and the clinical team. It clearly outlines recovery-related behaviors and the role of supports. The agreement should help with accountability and provides a structure to facilitate consistent implementation of treatment strategies (Hill et al., 2022). Drop-out rates will be tracked systematically. We have previously translated and adapted the TBT-S material to Norwegian and assessed its feasibility and acceptability with Norwegian participants (Stedal et al., 2023).

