### Sample size calculation

The sample size calculation is conducted based on the primary outcome, global EDE-Q score at 3-month follow-up. It is informed by data from a feasibility study conducted by the authors (Stedal et al., 2023), in which the *SD* of the change in global EDE-Q from baseline to post-treatment was 0.87. A between-group difference in global EDE-Q change of 0.44 was assumed, based on the study by Tregarthen et al. (2019), who defines 0.5*SD as a clinically relevant difference in change from baseline, corresponding to a medium effect size (Cohen’s *d* = 0.5). In a two-sided test of superiority with *α*-level = 0.05 and 80% power, a total sample size of 126 is required. Participants are allocated to study arms in a 1:1 ratio. To account for the observed correlation (*p* = 0.732) between baseline and 3-month follow-up as reported in our previous feasibility study (Skoog et al., 2025), an ANCOVA framework is employed in the sample size calculations using raw EDE-Q global score at 3-month follow-up while adjusting for baseline. Thus, the number of participants is multiplied by the factor (1 + *p*)/2. Applying the correlation *p* = 0.732, the multiplicative factor is (1 + 0.732)/2 = 0.866. This results in an estimated required sample size of 110 participants. Assuming 10% attrition rate, we will include a total of 120 participants.

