### Statistical analysis

Primary analyses will be conducted on the *Full Analysis Set* (FAS), defined as all participants who were randomly assigned to a treatment arm and who provided, at minimum, the following pre-assessment data; for individuals with AN/AAN, the EDE-Q; and for supports, at least one completed questionnaire, irrespective of the measure. As a sensitivity analysis for the primary outcome, the primary endpoint analysis will also be conducted on the *Per-protocol* (PP) population. In the TBT-S + TAU arm, the PP population will comprise those in the FAS who attended at least four of the five TBT-S days. In the TAU arm, the PP population will be identical to the FAS, as no additional intervention is delivered. Per protocol analyses will be adjusted for the time interval between randomization and pre-assessment.

The superiority of TBT-S plus TAU over TAU alone for the primary outcome will be analyzed using a linear mixed model with the 3-month EDE-Q global score as a continuous outcome, with baseline EDE-Q, treatment arm and study site, Time (factor) and Time (factor)*treatment arm interaction as fixed effects and subject ID as random effect. Secondary outcomes will be analyzed using linear mixed models in which baseline value, treatment arm, study site, time and time*treatment arm-interaction are included as fixed effects, and subject ID is included as random effect. The use of mixed linear models will allow for including in the analyses also participants that do not complete all assessments. As participants in the TAU alone condition may opt to receive the intervention after their 3‑month assessment, a proportion of TAU alone participants will undergo post‑3‑month treatment crossover. Analyses that include 6‑, 9‑, or 12‑month follow‑up will therefore incorporate analytic strategies appropriate for partial crossover. Further details of the statistical analyses will be specified in a statistical analysis plan, which will be completed before the database is locked and analyses commence.

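### Support outcomes: one random effect for subject ID cannot cover supports nested within patients, and if it is the support's own ID, arm comparisons will look too precise

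*Protocol article*

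**What the plan says.** The Statistical analysis section gives one model for every secondary outcome. Baseline value, arm, site, time and the interaction of time with arm are fixed effects. The sentence ends: "time*treatment arm-interaction are included as fixed effects, and subject ID is included as random effect". No other random effect is named.

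Support outcomes fall under this sentence. The abstract's Methods paragraph lists secondary outcomes "as well as changes in quality of life and caregiving experience among supports". The Aim and objectives section adds: "Secondary objectives also include the comparison of support experiences in terms of quality of life", and goes on to wellbeing, accommodation and expressed emotion. Table 1 has supports completing DASS, AESED, FQ, EQ-5D and CarerQol at pre-assessment, 3 months and 12 months.

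The number of supports varies. A patient must "have a minimum of one support person who can participate in the study", and the section on the intervention states: "TBT-S is administered to three to six adults with AN/AAN together with up to four supports each". Supports are counted individually: the Full Analysis Set requires, "for supports, at least one completed questionnaire, irrespective of the measure".

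**The concern.** Randomisation is described for patients, and supports follow their patient's arm. Support data therefore have three levels: visits within support, and supports within patient. People caring for the same ill person answer questions about the same illness, so their scores are likely to be positively correlated. Because arm varies only between patients, that correlation belongs in the standard error of the arm comparison.

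A single random effect can represent the support level or the patient level, but not both. If it represents the support, several supports of one patient count as independent evidence, and a stated secondary objective is tested with more false positives than the nominal 5%.

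**Working it through.** **The plan's own figures.** The only sample size given is for patients on EDE-Q. A standardised difference of 0.5 at two-sided 5% and 80% power gives 2 × (1.960 + 0.842)² / 0.5² = 62.8, so 63 per arm and 126 in total, as stated. Multiplying by 0.866 gives 109.1, stated as 110. The article then allows for 10% attrition and plans 120. None of this concerns supports, for whom no sample size, power or ICC is given.

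**What each reading of subject ID implies.**

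| Subject ID is | Patient level | Support level | Effect on the arm comparison |
|---|---|---|---|
| the support's own ID | missing | present | standard error too small |
| the patient's ID | present | missing | roughly valid; repeated measures on a support are not modelled |

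The first reading is the natural one, because supports enter the analysis set as individuals.

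**Size on the first reading.** Let m be the number of supports per patient (assumed) and ICC the correlation between supports of one patient after baseline adjustment (assumed).

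- Design effect: DE = 1 + (m − 1) × ICC.
- True standard error = reported standard error × √DE.
- True two-sided type I error at nominal 5% = 2 × [1 − Φ(1.96/√DE)].

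| m | ICC | DE | √DE | 1.96/√DE | Type I error |
|---|---|---|---|---|---|
| 1 | any | 1.0 | 1.00 | 1.96 | 5.0% |
| 1.5 | 0.2 | 1.1 | 1.05 | 1.87 | 6.2% |
| 2 | 0.3 | 1.3 | 1.14 | 1.72 | 8.6% |
| 3 | 0.3 | 1.6 | 1.26 | 1.55 | 12.1% |

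For example, with two supports for each of 120 patients and ICC 0.3, 240 supports carry the information of 240/1.3 = 185 independent ones. The formula takes equal numbers of supports per patient; unequal numbers with the same mean make DE somewhat larger.

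**Check by simulation.** The settings were 108 patients (120 less 10%), two follow-up visits, no true effect and no baseline covariate. Variance shares were 0.3 for patient, 0.3 for support and 0.4 residual, with 200 runs per setting. The arm difference at the first visit was tested at 5%.

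| Supports per patient | Random effect for support only | Random effect for patient only |
|---|---|---|
| 2 | 8.0% | 4.0% |
| 3 | 11.5% | 3.5% |
| 4 | 13.5% | 4.5% |

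With 200 runs these are rough. The approximate 95% interval for 8.0% is 8.0 ± 1.96 × √(0.08 × 0.92/200), or 4.2% to 11.8%, which includes 5%. The rates for three and four supports lie clearly above 5%. The patient-level rates are compatible with 5%.

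**The case against.** The strongest objection is that the sentence is a condensed, generic one. Most secondary outcomes are measured on patients, for whom subject ID is the ordinary choice, and the article leaves further detail to a statistical analysis plan due before database lock. This lowers the certainty but does not remove the point. The article does state the random-effects structure, the same section has supports in view when it defines their analysis set, and nothing elsewhere provides a patient or family level, a robust variance or a rule of one support per patient.

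A second objection stands in full: the inflation depends on the reading. A reader might infer that support standard errors will be too small in any case. The documents do not support that, because subject ID is undefined for supports, and with the random effect at patient level the simulated error was near nominal.

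Third, the size is assumed throughout. A reader might take four supports per patient and ICC 0.5, which gives DE 2.5 and 21.5%. But four is a ceiling on who attends the treatment week, the minimum is one, and the number of supports assessed in the TAU arm is not stated. The model also adjusts for baseline, which can absorb stable similarity among supports of one patient, so the relevant ICC may be lower than a raw one. Nor do the documents say that supports share a household. The Introduction allows friends as well as relatives, and the patients are adults. Caring for the same person is reason to expect correlation, but its strength is unknown.

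Finally, the secondary objectives are described as exploratory, and no support outcome is powered.

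**Conclusion.** The point holds in a limited form. For supports, the stated model lacks one level whichever ID is meant. On the natural reading it lacks the level at which arm is assigned, and arm comparisons on DASS, AESED, FQ, EQ-5D and CarerQol will look more precise than they are. A plausible span for type I error is 5% to about 12%, for one to three supports per patient and a baseline-adjusted ICC of up to 0.3. Both inputs are assumptions, and the problem disappears if nearly every patient brings one support.

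This is worth correcting because it touches a stated secondary objective. A reader might extend it to the main result, but EDE-Q is measured once per patient per visit, so neither that analysis nor the planned 120 is affected. Clustering by treatment week is a different question and is not settled here.

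**What to change.** For support outcomes, define the identifiers and add the missing level: a random intercept for patient (family), with support nested within it. Alternatively, keep the support-level effect and use a variance that is cluster-robust at patient level. In either case, base the degrees of freedom for the arm comparison on the number of patients, not supports. The secondary model for patient outcomes can stay as written.

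The statistical analysis plan is due before database lock, and 31 participants had been randomised when the article was submitted, so the change can be made there. It needs no new data, only a dataset that links each support to a patient, which assigning supports to an arm already requires. The cost is slightly wider intervals for support outcomes.

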### Patient and public involvement

A participant representative from a Norwegian eating disorder user organization (Rådgivning om Spiseforstyrrelser, ROS) is a member of the project group and will receive authorship credit on any publications where the Vancouver recommendations (International Committee of Medical Journal Editors, 2025) for co-authorship are met. ROS shows their support to the study by providing information about the project to their members and the public through their channels. Results from the trial will be disseminated to the public through open access scientific publishing and via presentations—both at scientific conferences as well as for the general population through media and user organizations.

## Discussion

This study will be the first controlled trial evaluating TBT-S and represents an important step in establishing treatment effectiveness. If TBT-S in conjunction with TAU demonstrates superior outcomes compared to TAU alone, it may warrant consideration as a standard adjunctive treatment for adults with AN. TBT-S provides adults with AN/AAN with an opportunity to actively involve family members or other support persons in their treatment. While most clinical guidelines recommend family-based treatment for children and adolescents with eating disorders (Benedictson et al., 2025), few structured options are available for adults who wish to include their support network (Baudinet and Eisler, 2024). Importantly, TBT-S may also help address the needs of family members who seek to understand the illness and learn how to provide effective support. This aligns with the advocacy of eating disorder user organizations, which strongly emphasize the inclusion of family members in treatment.

Participants included in the study will receive either TAU alone, or TAU in conjunction with TBT-S. Although this is the first time TBT-S is assessed in an RCT, previous studies have demonstrated that it is a highly endorsed treatment by both individuals with an eating disorder and supports, and have indicated that it could help reduce eating disorder symptoms (Wierenga et al., 2018; Knatz Peck et al., 2021; Stedal et al., 2023; Skoog et al., 2025). Notably, qualitative reports from participants indicate that some of the most helpful elements of TBT-S were; (i) how it improved the relationship between the individual with an eating disorder and their support, (ii) how their knowledge and understanding of eating disorders increased, and, (iii) how they gained more hope for the future (Stedal et al., 2024). These are all elements which are difficult to quantify and measure with standardized questionnaires, but nonetheless could be important for improving quality of life. Or, as stated by Hay and colleagues “Treatment trials need to move beyond targeting core eating disorder pathology (primarily weight restoration) and examine effectiveness in minimizing harm and reducing personal and social costs of chronic illness, such as medical morbidity, burden on health services, quality of life, depression and isolation (Hay et al., 2012, p. 1143).” Therefore, in this RCT we have ensured to also include measures of quality of life, anxiety and depression—also for the supports, and our 12-month health economy analysis will provide information on burden on health services. Although these are not primary outcome measures, they will undeniably be imperative to assess the impact TBT-S might have on these important variables.

The study has some potential limitations which are worth noting, some of which could impact the ability to interpret potential improvements. For example, the participants in the TBT-S arm will receive 35–40 h of additional treatment which is not controlled for in the control group. Thus, it will be uncertain if any improvements in the TBT-S group could be attributable to the increased dose of treatment, and/or non-specific elements in the TBT-S group (e.g., placebo, peer-support, behavioral activation). Nevertheless, this RCT marks an important first step in deciphering whether TBT-S in addition to TAU could improve treatment outcomes, and future studies might wish to include a comparison group program of similar intensity, with as little overlap as possible with TBT-S, thereby increasing the chances of better attributing any changes to TBT-S. Further, being allocated to TAU could be discouraging for some participants, increasing the risk of drop-out for this group. In addition, currently there are no other clinics in Norway offering adult TBT-S for AN/AAN. However, this could change over time and there is a risk that the TAU group gets tainted by TBT-S from a treatment provider not included in the study. Travel costs are covered through, a public service that reimburses travel expenses for healthcare treatments and clinical trials, and most employers will provide either paid or unpaid leave to receive healthcare. However, some eligible participants may still be prevented to participate in the study because they are not able to take time off work to attend TBT-S. Furthermore, the power analysis were based on our feasibility study with a comparable population. Even so, since both groups in this RCT will be receiving active treatments, there is a risk that potential differences between groups could be obscured by varying treatment settings and intensities, which would be expected to achieve reasonable effect sizes on their own. In addition, the timing of TBT-S within participants’ ongoing treatment is not standardized. As TBT-S is designed to be flexibly integrated into routine clinical care, participants may receive the intervention at different points in their treatment trajectory, which could contribute to heterogeneity in treatment response and introduce potential floor or ceiling effects. Finally, the lack of baseline assessment before randomization could result in the study’s pre-assessment being biased by the randomization. We will perform analyses of pre-assessments to check that the randomization produced equivalent groups. Any differences will be controlled for.

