## Method

### Study design

We will conduct a non-blinded, randomized, controlled, parallel-group, superiority trial comparing (i) TBT-S plus TAU to (ii) TAU only. Similar control conditions have been used in previous trials of short-term interventions for eating disorders (e.g., Godart et al., 2012; Gowers et al., 2010; Quiles et al., 2025). Four main assessments will be conducted: pre-assessment, post-assessment, and 3- and 12- months follow-up. Eating disorder service utilization during the preceding 3 months will be assessed at pre-assessment and at 3-, 6-, 9-, and 12-months follow-ups. See Figure 1 for Consolidated Standards of Reporting Trials (CONSORT) flow chart (Hopewell et al., 2025) of the trial. The project will be arranged as a multisite study with two collaborating units (Regional department for eating disorders (RASP) at Oslo university hospital and the Department of eating disorders (RAS) at Haukeland university hospital). The collaborating clinics offer TBT-S as part of their standard clinical practice. In accordance with the treatment manual (Hill et al., 2022) there are no requirements regarding the specific time point during the ongoing treatment at which TBT-S should be introduced; clinicians can integrate TBT-S flexibly into ongoing therapy. Thus, the timing of TBT-S within TAU is individualized rather than standardized and depends primarily on practical considerations, including participants’ ability to take time off for the 5-day intervention and the scheduling of TBT-S weeks at the treatment sites (4–6 times per year). Multiple participants are assigned to each TBT-S week before being randomized to receive TBT-S plus TAU or TAU only. Participants randomized to TAU only complete assessments at the same time-points as those randomized to the corresponding TBT-S week, ensuring comparability across study arms.

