### Randomization and concealment

Included participants will be randomized using Viedoc, an online data collection platform hosted by Oslo University Hospital, Norway, approved by the data protection department at Oslo University Hospital, and monitored by a third party, the Clinical Trials Unit at Oslo University Hospital. This solution is adapted for randomization and gathering participant-reported data via PC, mobile or tablet. The Clinical Trials Unit has generated the randomization sequence in Viedoc which is stratified by treatment location and balanced by being built up of blocks of 2, 4 and 6 occurring in random order. Participant data will be identified by their assigned ID number rather than by name, the Norwegian identifier list will be stored in MedInsight, a Regional committees for Medical and Health Research approved digital participant list solution. All personal data will be stored on encrypted servers, requiring VPN-connection and/or two-step authentication (digital data) in accordance with data management guidelines from regional and local authorities.

Dates for TBT-S treatment weeks will be announced during advertisements so that participants can declare interest and availability for specific treatment weeks in advance of randomization. Allocation to TBT-S treatment groups (specific weeks) is based on the order in which participants declare interest and availability. Due to the nature of the intervention of this study, blinding of participants is impossible. Assessors are also not blinded, but are not included in the delivery of the intervention.

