### Measurements

Table 1 provides an overview of interviews and self-report assessments at the different time points. Within 14 days before the start of a TBT-S-week, clinician-administered interviews will be conducted, and pre-assessment forms will be completed in both treatment arms. Post-assessments will be completed within 12 days after the last day of the TBT-S week and follow-up assessments within a 20 day period centered at 3-, and 12 month follow-ups. Use of health care services will be assessed at pre-assessment and at 3-, 6-, 9-, and 12-months follow-ups. The primary endpoint will be the group difference in change in eating disorder psychopathology (Eating Disorder Examination Questionnaire [EDE-Q (Fairburn and Beglin, 1994)] Global score) from pre-assessment to 3- month follow-up. The Norwegian version of EDE-Q has shown satisfactory psychometric properties (Rø et al., 2015; Reas et al., 2011). Interviews performed at pre-assessment are the Mini International Neuropsychiatric Interview [M.I.N.I. 7.0.2 (Sheehan et al., 1998)] and the Eating Disorder Assessment for DSM-5 [EDA-5 (Sysko et al., 2015; Dahlgren et al., 2020)] which are administered to assess comorbidities and confirm the AN/AAN diagnosis self-reported by the patient. When travel time to the main recruitment site (Oslo university hospital) allows for in-person assessments, participants are invited to fill out the forms on site, where weight and height will also be measured and registered. All other participants will complete the self-report assessments remotely and self-report weight and height. The M.I.N.I. and EDA-5 interviews of these patients will be conducted via a secure digital video platform. The main tools used for assessment are all previously validated and well-established measures (Akoury et al., 2018; Bouwmans et al., 2013; Cejalvo et al., 2025; Dambi et al., 2018; Feng et al., 2021; Fowler et al., 2014; Gratz and Roemer, 2004; EuroQol Group, 1990; Hibbs et al., 2014; Hoefman et al., 2013; Håseth et al., 1990; Osman et al., 2012; Pedersen et al., 2022; Sepulveda et al., 2009; Spielberger, 1970; Timman et al., 2015; Wiedemann et al., 2002; Winkler et al., 2019). Utilization of health care services and data on resource use will be collected using the self-reported Treatment Inventory of Costs in Patients with psychiatric disorders (TIC-P) questionnaire (Bouwmans et al., 2013; Timman et al., 2015). To ensure a detailed characterization of TAU, additional items on eating disorder service utilization have been added. These include whether the participant is currently receiving ED treatment, level of care and treatment intensity, as well as type of therapy and treatment modality. This information on service utilization together with the EuroQoL 5D [EQ-5D (Feng et al., 2021; Group, 1990)] and the Care-related Quality of Life instrument [CarerQol-VAS (Cejalvo et al., 2025)] will be used to assess the potential cost-effectiveness of TBT-S. Cost will be examined from both the healthcare provider as well as the societal perspective. Norwegian translations of all measures will be used. Two of the measures (Accommodation and Enabling Scale for Eating Disorders and Eating Disorder Quality of Life Scale) have not been validated in Norwegian. TBT-S attendance will be assessed at post-assessment (TBT-S plus TAU group only) using a study specific question added to the Client Satisfaction Questionnaire, asking participants to report how many of the five TBT-S treatment days they attended. At the 3- and 12- month follow-ups, adherence to TBT-S treatment recommendations will also be assessed using self-report measures, including the extent to which participants who received TBT-S have utilized the treatment tools provided during the treatment week.

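### The promise to control for any pre-assessment difference opens the fixed covariate list and can adjust for effects of allocation itself

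*Protocol article*

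**What the plan says.** The Statistical analysis section fixes the primary model: a linear mixed model for EDE-Q global "with baseline EDE-Q, treatment arm and study site, Time (factor) and Time (factor)*treatment arm interaction as fixed effects", with subject as random effect. Secondary outcomes have a matching closed list: "baseline value, treatment arm, study site, time and time*treatment arm-interaction are included as fixed effects".

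The limitations part of the Discussion then adds an open-ended rule: "We will perform analyses of pre-assessments to check that the randomization produced equivalent groups. Any differences will be controlled for". It stands directly after the admission that "the lack of baseline assessment before randomization could result in" a pre-assessment biased by the randomization.

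Other sections bear this order out:

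- Study design: "Multiple participants are assigned to each TBT-S week before being randomized to receive TBT-S plus TAU or TAU only".
- Measurements: "Within 14 days before the start of a TBT-S-week, clinician-administered interviews will be conducted", with the pre-assessment forms completed in the same window in both arms.
- Randomization and concealment: "blinding of participants is impossible. Assessors are also not blinded".
- Discussion: "being allocated to TAU could be discouraging for some participants".

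**The concern.** There are two difficulties.

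First, an unrestricted promise to control for whatever differs cannot describe the same analysis as a closed covariate list. Whoever runs the analysis would have to choose which text to follow, and which differences count, after seeing data by arm.

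Second, the remedy does not suit the problem it is offered for. Checking baseline equivalence makes sense only for variables that allocation cannot have touched. Here the participant may already know the arm when rating motivation, anxiety or impairment. A difference could be chance or a reaction to the allocation, and the check cannot tell these apart. If it is a reaction, the measure is not a confounder, and conditioning on it can move the treatment estimate away from the effect of being offered TBT-S. At stake are the pre-specification and the interpretation of the primary estimate.

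**Working it through.** The article gives no figure for this point. Its sample size chain (126, then 126 × 0.866 = 109.1, taken as 110, then 120 with attrition) adjusts for baseline EDE-Q only, so the point does not alter it.

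**Step 1. How often would the rule be triggered by chance?** Table 1 lists 13 patient measures at pre-assessment apart from the diagnostic interviews: BMI and 12 questionnaires including EDE-Q. That leaves 12 besides EDE-Q. The article states no criterion; assume one test each at 5%. With perfect randomization:

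- independent measures: 1 − 0.95^12 = 0.46
- pairwise correlation 0.3 (simulated): 0.40
- pairwise correlation 0.5 (simulated): 0.32

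**Step 2. Does this harm error rates if differences are only chance?** Simulation: 110 participants, 12 extra measures, all inter-correlations 0.5, outcome in SD units = 0.55 × baseline EDE-Q + 0.3 × mean of the other measures + noise of SD 0.62 − effect. A fixed model (arm and baseline EDE-Q) is compared with one that adds every measure with p < 0.05 at baseline.

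| No allocation shift | Fixed | Check and adjust |
|---|---|---|
| Type I error | 4.9% | 4.7% |
| Power (effect 0.35) | 80.3% | 79.9% |

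The answer is no. The selection looks at baseline data, not at outcomes.

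**Step 3. What if allocation shifts the other measures?** The size of any shift is not given; 0.2 and 0.4 SD in favour of TBT-S are assumed, with EDE-Q itself unshifted.

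*(a) The shift carries through to the 3-month outcome.*

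| Shift | Estimate, fixed → adjusted | Power, fixed → adjusted |
|---|---|---|
| 0.2 SD | 0.41 → 0.36 | 91% → 80% |
| 0.4 SD | 0.47 → 0.35 | 97% → 74% |

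*(b) The shift is transient and gone by 3 months.* The fixed model is then unbiased. Check-and-adjust is biased by about 0.04 SD (shift 0.2) to 0.10 SD (shift 0.4). Power falls from 80% to 68% or 46%, and at 0.4 SD type I error rises to 11%. A rerun with exactly the Step 2 coefficients gave bias 0.05 and 0.12 SD, power 67% and 41%, and type I error 7% and 15%, so these figures depend on the outcome model assumed.

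In EDE-Q points: SD of change 0.87 and correlation 0.732 imply, with equal SDs at both visits, a raw SD of 0.87/√(2 × (1 − 0.732)) = 1.19. A bias of 0.04 to 0.10 SD is then 0.05 to 0.12 points, or 11% to 27% of the 0.44 target.

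**Step 4. The covariate already in the model.** Baseline EDE-Q is collected at the same visit. With slope 0.732 (equal SDs assumed), an allocation shift of b points moves the adjusted estimate by 0.732 × b:

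| b | Movement | Share of 0.44 |
|---|---|---|
| 0.1 | 0.07 | 17% |
| 0.2 | 0.15 | 33% |
| 0.3 | 0.22 | 50% |

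This arises in the pre-specified model, with or without the disputed rule.

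**The case against.** The sentence stands among the limitations, names no significance test and no threshold, and does not mention the primary model. Further details are deferred to an analysis plan to be completed before database lock, and a sensitivity analysis could satisfy the wording. All of this is true. Applying the rule to the primary model is a reading of unqualified text, and the 5% criterion is this review's assumption. Two of the 12 rows (TIC-P and the eating disorder service items) are service-use inventories, so one test per row is itself a simplification. What does not fall away is that the sentence is a positive, unrestricted commitment, offered as the remedy for a bias in the pre-assessment. It is not merely a detail left for later.

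A reader might infer that nominal error rates fail in general under such a rule. Step 2 does not support that: for chance imbalance they hold. Error rates suffer only if allocation has shifted the measures.

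One might also argue that a reaction to allocation is a nuisance worth removing. But if the reaction has faded by 3 months there is nothing to remove and adjustment introduces bias. If it persists, it is arguably part of the effect of the offer. Adjusting for whichever measures happen to differ settles neither case.

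**Conclusion.** The point holds in a limited form. The rule conflicts with the closed covariate list if read as written, and it cannot do what it is offered for, because pre-assessment follows unblinded randomization.

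Under pure chance the cost is to pre-specification only: a 32% to 46% chance that at least one measure would qualify, given the assumed 5% criterion and correlations from 0.5 down to 0. Under an allocation shift the estimate can be biased materially. The sizes in Step 3 rest on assumed shifts and an assumed outcome model. Their direction reverses if allocation to TBT-S worsens pre-assessment scores instead of improving them.

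The documents do not establish that the primary model will be changed, that significance tests will be used, or that a shift occurs; the article says only that it could. Nor would deleting the rule cure the underlying problem, since baseline EDE-Q shares it (Step 4).

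**What to change.** - Delete the two sentences that set the check-and-control rule.
- State that pre-assessments will be described by arm, without tests.
- Keep the primary model to the covariates in the Statistical analysis section, plus any prognostic variable named in the analysis plan before data are seen, preferably one that allocation cannot affect.
- Label any model with further covariates as a sensitivity analysis.
- Say plainly that baseline EDE-Q is also measured after randomization, so that the primary estimate is read with this in mind.

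The cost is a few sentences, with no change to the sample size. It can still be done in good time: 31 participants had been randomized at submission and inclusion runs to December 2027. Removing the problem for baseline EDE-Q would require measurement before allocation is disclosed. That is a change of design and is not part of this fix.
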